### Primary and secondary outcome measures

#### Primary outcomes

The primary outcome measures for comparison in this trial will be the coverage of key protective, preventive and curative quality coverage indicators for pneumonia, diarrhea, and malaria (Table 1). These quality and coverage indicators have been found to be the most effective interventions for pneumonia, diarrhea, and malaria across the protective, preventive and curative spectrum, and at community/family and health-facility/health care worker-level deaths.

#### Secondary outcomes

Other outcome measures that will be evaluated include the prevalence of pneumonia, diarrhea, and malaria amongst the target under-5 year age group. These might be suggestive of the status of protective and preventive interventions. Mortality impact will be a secondary indicator and will be modeled using the Lives Saved Tool (LiST) since reliable child mortality data is lacking at the district level and we are unable to measure it in this project [20]. We will also document the immediate management outcomes in the intervention arm such as the presence of annual reports that reflect priority bottlenecks for pneumonia, diarrhea, and malaria as determined by the bottleneck/causal analysis intervention tools. This will reflect the level of adherence to the intervention and to get a sense of how well the subgroup that carried out the intervention as intended was successful on the outcome indicators.

#### Data collection and analysis plan

Primary data collection will use parallel community (household) LQAS questionnaire-based surveys conducted in both intervention and control districts at baseline, midterm (2 years later), and at endline. In order to be pragmatic and to suit the Uganda Child Survival Package, in the intervention districts these LQAS surveys will also be the primary tool for collecting information to be used in the BNA. Each of the 16 districts included in the cluster randomized trial will be divided into five strata (supervision areas) and, based on a sample list of villages from the Uganda Bureau of Statistics (UBoS) for each strata, 19 villages will be randomly selected based on number of households per village using Probability Proportional to Size (PPS) methodology. A total of 760 individuals of each study target respondent group will be included in both the intervention and control arms.

In each village, a random reference household will be selected using a table of random numbers applied to a village household list or village sketch map, and the next nearest door to this will determine the first and subsequent household from which one randomly selected respondent from each of the target populations will be sought for interview with a maximum of one respondent from each household regardless of category.

The household LQAS surveys will focus on seven target population groups including mothers of children under 6 months, mothers of children 6–11 months, mothers of children 12–23 months, mothers of children under 5 years, mothers of children under 5 years with diarrhea in the last 2 weeks, mothers of children under 5 years with acute respiratory tract infections in the last 2 weeks and mothers of children under 5 years with fever in the last 2 weeks, resulting in 19 individuals from each target population group from each village (Fig. 1).

Information indicating adherence to CODES intervention will be based on documentation reports from the support implementing partners (CFI/LSTM and ACODE). To evaluate community participation and changes in demand side perceptions and behavior we will collect data by short messaging service (SMS) survey polls, LQAS surveys, and focus group discussions (FGDs).

Primary analysis for the cluster randomized trial will use an intention-to-treat approach to districts as either allocated to intervention or control group. We will conduct a difference of differences analysis of proportions of the key quality coverage indicators looking at differences between baseline and endline survey estimates for the intervention and for the control district areas. The analytical techniques used will appropriately take into consideration the clustering design effects due to the cluster randomized design, as well as any weighting factors, using techniques that will include but not be limited to generalized estimating equations (GEE) with analysis of covariance (ANCOVA).

Secondary analysis will look at a subgroup of districts that are deemed to have “performed well” on the basis of immediate outcomes (such as the annual report) to see if there is any indication of “dose-response.” Similarly, subgroups of vulnerable populations will be evaluated for coverage in an equity analysis. Based on the coverage achieved in the intervention and comparison districts, we will model the estimated lives saved using the LiST. Process indicators and contextual factors will also be documented to aid in the interpretation of the findings. To evaluate changes in management behavior among the DHMT, data collection will include participant observation, in-depth interviews with stakeholders, and analysis of documents such as district health plans and implementation monitoring reports. Qualitative data will be analyzed using content analysis.

Ethical clearance for the project was given by Uganda National Council for Science and Technology (Ref:SS2548). All districts will implement the Uganda Child Survival Strategy as per the Health Sector Strategic Plan. Informed consent will be obtained from each study participant after explaining the objectives of the study and procedure. Confidentiality of interviewees will be maintained. A study Steering Committee chaired by the Ministry of Health and involving key partners and the study teams has been set up to facilitate policy linkage. The Steering Committee meets quarterly.

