## Methods

### Trial design

This is being implemented as a cluster randomized controlled trial with eight districts (clusters) as intervention and eight other districts as comparison districts. All the then 111 districts in Uganda were assessed for eligibility, but 81 of those did not meet the eligibility criteria of having a high burden of child mortality threshold as set by United Nations Children’s emergency Fund (UNICEF). Five eligible districts with a high mortality (clusters) that were involved in the proof-of-concept phase of the CODES intervention were also excluded for consideration in the randomization district sampling frame. At the analytical level all the individuals as defined by the respective target groups will be eligible for analysis.

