### Sample size calculations

Based on the CODES pilot in five districts, and also according to data from the Uganda Demographic Health Surveys, the estimated baseline levels for the various key coverage and quality indicators for malaria, diarrhea and pneumonia ranged from 2 to 85 %. On the basis of these baseline estimates, sample size estimates were computed with a goal to achieve 80 % power of observing a greater than 25–30 % (regarded to be of public health significance) absolute difference in increase in various outcome indictors between intervention and control groups at the 5 % significance level (and assuming the typical level of intra-cluster correlation of 0.07 associated with most of the indicators). The computations revealed that a minimum of four districts (with each district providing a fixed LQAS-based evaluable sample of 95 individuals for each of the relevant target population) would have to be randomized per CODES study arm to address the primary objective assuming this cluster randomized design [8].

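### Run with its default robust variance and z reference, the named GEE analysis would not hold the 5% level with only eight districts per arm (about 9–11% if matching is uninformative)

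*Protocol article*

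**What the plan says.** Under Trial design, the protocol article describes a "cluster randomized controlled trial with eight districts (clusters) as intervention and eight other districts as comparison districts". Trial setting and randomization adds that the districts form eight matched pairs, with a coin toss deciding the arm within each pair.

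Sample size calculations sets the comparison "between intervention and control groups at the 5 % significance level". It does not say whether the test is one- or two-sided. It takes 95 people per district and target group, "assuming the typical level of intra-cluster correlation of 0.07 associated with most of the indicators".

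Data collection and analysis plan specifies an intention-to-treat difference of differences in indicator proportions, baseline to endline. It promises suitable handling of clustering and weights, "using techniques that will include but not be limited to generalized estimating equations (GEE) with analysis of covariance (ANCOVA". No variance estimator, reference distribution or degrees of freedom is given, and the section does not say whether the pairs enter the model. The full protocol and analysis plan are not at hand.

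**The concern.** The sandwich variance in GEE is justified as the number of clusters grows. With eight per arm two things go wrong in the default test. The sandwich variance is biased downward, because it uses residuals around fitted arm means without correcting for having estimated them. The normal reference also treats that variance as known, although it rests on about 14 degrees of freedom. Adjusting for baseline district coverage, which is a natural reading of the ANCOVA element, uses up further information and adds to the problem.

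The effect estimates themselves are not affected. Their p-values and confidence intervals are, and the same test would be applied to each of the coverage indicators that make up the primary outcome. Intervals that are too narrow would make an improvement in coverage look better established than it is.

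**Working it through.** **Inputs from the article.** Eight districts per arm; 5% level; 95 people per district and target group; intra-cluster correlation (ICC) 0.07; baseline coverage that "ranged from 2 to 85" per cent; power target 80%; a difference of 25–30 points.

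**Assumptions not in the article.** Two-sided test; equal district sizes; baseline-to-endline correlation of district effects from 0 to 0.8; ICC of 0.01 as well as 0.07; within-pair correlation from 0 to 0.5.

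**The plan's own figure first.** The stated minimum is four districts per arm.
- Design effect: 1 + (95 − 1) × 0.07 = 7.58.
- A 30-point difference at the least favourable baseline (35% to 65%) needs 43 people per arm under simple randomization with the normal-approximation formula for two proportions. Then 43 × 7.58 / 95 = 3.43, which rounds up to 4.
- At 25 points (37.5% to 62.5%) it needs 62 people, and 62 × 7.58 / 95 = 4.95, which rounds up to 5.

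The stated four therefore reproduces at the 30-point end. The formula uses normal quantiles and makes no allowance for few clusters. This fits large-sample reasoning but does not show how the final test will be run.

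**Default GEE, difference of differences, matching uninformative.** Let d be a district's change from baseline to endline, and k = 8.
- Sandwich variance of an arm mean: Σ(d − d̄)² / k².
- Unbiased variance: Σ(d − d̄)² / [k(k − 1)].
- Ratio: (k − 1)/k = 7/8.
- Rejecting when the sandwich z exceeds 1.96 is the same as rejecting when the ordinary two-sample t exceeds 1.96 × √(7/8) = 1.833.
- Type I error: 2 × P(t₁₄ > 1.833) = 0.088.

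**Simulation with no true effect.** District means: 60,000 runs per scenario, beta-binomial, coverage 10% to 85%. Individual-level logit GEE: 1,000 runs per scenario at 30%, 50% and 85% coverage; near a 10% rejection rate the Monte Carlo standard error is √(0.1 × 0.9 / 1000), about 0.9 points.

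| Test | District means | Logit GEE |
|---|---|---|
| Difference of differences, sandwich, z | 8.6–9.0% | 8.2–10.4% |
| Baseline-adjusted, sandwich, z | 10.0–10.8% | 9.6–11.6% |
| Mancl-DeRouen-type SE, z | 5.1–5.7% | 5.1–7.1% |
| Mancl-DeRouen-type SE, t₁₄ | not run | 4.1–5.5% |
| Kauermann-Carroll-type SE, t₁₄ | 4.5–5.2% | not run |
| t-test on 16 district changes | 4.5–5.2% | not run |
| Paired t-test on 8 pairs | 4.6–5.3% | not run |

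**Half-corrections (analytic).** An unbiased variance with z gives 2 × P(t₁₄ > 1.96) = 7.0%. The uncorrected sandwich with t₁₄ gives 2 × P(t₁₄ > 2.145 × √(7/8)) = 6.5%. Respecting the pairs without any correction gives 2 × P(t₇ > 1.833) = 10.9%.

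**Informative matching, pairs ignored in the model** (400,000 runs of normally distributed district changes):

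| Assumed within-pair correlation | Sandwich, z | Kauermann-Carroll, t₁₄ |
|---|---|---|
| 0 | 8.8% | 5.0% |
| 0.1 | 7.4% | 4.0% |
| 0.2 | 6.1% | 3.2% |
| 0.3 | 4.7% | 2.3% |
| 0.5 | 2.4% | 1.1% |

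A corrected test that ignores informative pairs stays below 5% but is conservative, which costs power.

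**The case against.** The strongest reply is that the article never specifies the test that fails. It undertakes to handle clustering suitably, offers GEE with ANCOVA as a non-exclusive example, and is silent on the variance estimator and reference distribution. Those details usually belong in an analysis plan, and their absence from a journal article is not an error. Both remedies below are compatible with the text as it stands.

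A reader might infer that the plan omits a small-sample correction and so has a true type I error of 9–11%. The documents do not support that. The figure requires three things together: an uncorrected sandwich, a normal reference and uninformative matching. The districts were matched on region, recent creation, quality-improvement activity and potential to reduce child mortality. If that matching carries information and the pairs are ignored, the same test may reject less often than 5%. Nor is it established that every primary interval would be too narrow.

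These objections stand against the stronger reading and limit severity. They do not remove the point. Default GEE already counts as accounting for clustering, so the promise in the text does not exclude the version that inflates the error. The non-exclusive wording adds alternatives without removing that version. The article supplies no within-pair correlation, so matching cannot be relied on to protect the level.

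**Conclusion.** The concern holds in conditional form. With eight districts per arm, the only named technique, run in its default form with uninformative matching, has a two-sided type I error of about 9% for the difference of differences (8.8 / 5, or 1.8 times nominal) and about 10–11% with baseline adjustment (2.0 to 2.2 times nominal). With pairs ignored and matching informative, the error falls to about 6.1% at an assumed within-pair correlation of 0.2 and 2.4% at 0.5. The level is therefore set by an unknown correlation rather than by design.

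The analytic 8.8% rests on a two-sided test, equal districts and normally distributed district changes; the simulations show that it barely moves across the coverage levels and correlations tried. This is a matter to settle before the endline data are analysed, not a demonstrated error in what the article states.

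**What to change.** Name the primary test in one sentence, choosing one of:

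- GEE with a bias-corrected sandwich (for example Kauermann-Carroll or Mancl-DeRouen) and a t reference on district degrees of freedom, stating whether the pairs enter the model. Both the variance and the reference need correcting.
- A district-level analysis of the 16 baseline-to-endline changes that reflects the eight pairs: a paired t-test on 7 degrees of freedom, or the exact within-pair permutation test over 2⁸ = 256 allocations. The latter follows the coin-toss design directly; its smallest two-sided p-value is 2/256 = 0.008.

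No new data are needed. The cost is wider intervals than default GEE would report. With t₁₄ and the unbiased variance the factor is (2.145 / 1.96) × √(8/7) = 1.17, about 17% wider. With 7 degrees of freedom it is (2.365 / 1.96) × √(8/7) = 1.29, about 29% wider at equal between-district variance; informative matching would recover some of that. If the full protocol or analysis plan already specifies such a test, citing it is enough.

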## Discussion

Previous studies have highlighted the poor institutional capacity in decentralized health systems of developing countries [7, 21–23]. Decentralization in Uganda had the objective of bringing political power closer to local communities to respond to local needs, build local capacity, and improve accountability However, there are major constraints in the implementation of health interventions by district health management teams. CODES aims to increase coverage of effective interventions by increasing DHMT capacity to prioritize and implement context-specific solutions, and by empowering communities to become active partners in diagnosis and monitoring barriers to access and quality service provision, as well as in the equity of utilization.

If the CODES intervention is successful, an increase in effective coverage of child survival interventions is expected, and this should be associated with reductions in child mortality. We designed the main CODES trial after an initial pilot in five districts. This pilot phase enabled us to learn how to adopt, adapt, and harmonize the project intervention components which we are now testing using a controlled design.

However, we are aware that our design has limitations associated with the measurements and data collection techniques. The use of multiple data sources, i.e., government administrative databases as a source for supply side data and surveys as a source for demand side data, might produce different patterns of utilization and availability of services. For instance, a household survey will capture people that received service regardless of the type of provider (public or private), while administrative databases will provide only public sector data. Another limitation is the use of LQAS methodology to collect data. This data collection technique does not produce point estimates of coverage. It typically can be used only to assess the coverage in relation to a pre-established cut-off in each “lot.” However, at district and overall randomization arm level it is possible to calculate a coverage level by weighting the population size of each sub-district and aggregating these data together. In addition, we choose to use LQAS as the government and partners in the country are scaling up its use.

The novelty of the current proposal is that it represents a combination of several tools previously implemented individually (often at national level) in an integral way in order to systematically address bottlenecks on supply and demand sides to implement strategies to reduce child morbidity and mortality at district level. It differs from previous approaches in that it is focused on priorities, on specific bottlenecks to implementation, and on local managerial gaps and evidence-based solutions. The lessons learned on strengthening district-level managerial capacities in both existing and new districts as well as on mechanisms for community monitoring will have implications not only in Uganda but also in other similar settings. To motivate early adoptions of lessons learned, CODES has a Steering Committee chaired by the Ministry of Health and sits quarterly to share experiences.

### Trial status

By the time of submitting this manuscript, the trial was at the intervention stage having successfully implemented the proof-of-concept stage during the first 2 years. Currently the intervention is in its final year.

## Abbreviations

ANCOVA: analysis of covariance
BNA: Bottleneck Analysis
CBOs: Community-based Organizations
CFI: Child Fund International
CODES: Community and District Empowerment for Scale-up
CQI: Continuous Quality Improvement
DBA: District Bottleneck Analysis
DHMT: District Health Management Team
FGD: focus group discussions
GEE: generalized estimating equations
LiST: Lives Saved Tool
LQAS: Lot Quality Assurance Survey
LSTM: Liverpool School of Tropical Medicine
MDGs: Millennium Development Goals
MFI: Model For Improvement
PPS: Probability Proportionate to Size
SSA: sub-Saharan Africa
UBoS: Uganda Bureau of Standards
UNICEF: United Nations Children’s Emergency Fund
WHO: World Health Organization
